### Non-investigational products

#### *Albendazole*

Albendazole is a benzimidazole anthelmintic agent highly effective against a wide range of intestinal helminths and, at higher doses, against tissue helminth infections. Albendazole exhibits larvicidal, ovicidal and vermicidal activity, and is thought to act via inhibition of tubulin polymerization. This causes a cascade of metabolic disruption, including energy depletion, which immobilizes and then kills the susceptible helminth. Albendazole is poorly absorbed from the gastrointestinal tract due to its low aqueous solubility. Oral bioavailability appears to be enhanced when albendazole is co-administered with a fatty meal (estimated fat content 40 g) as evidenced by higher (up to five-fold on average) plasma concentrations of albendazole sulfoxide as compared to the fasted state. Plasma concentrations of albendazole sulfoxide increase in a dose-proportional manner over the therapeutic dose range following ingestion of a fatty meal (fat content 43.1 g). The mean apparent terminal elimination half-life of albendazole sulfoxide typically ranges from 8 to 12 hours in normal subjects. Albendazole sulfoxide is 70% bound to plasma protein and is widely distributed throughout the body. Following oral administration, albendazole has not been detected in human urine. Biliary elimination presumably accounts for a portion of the elimination [32].

Albendazole is used in children of 1 to 2 years at one oral 200 mg dose and in adults and children older than 2 years at 400 mg in one oral dose. Albendazole will be given at enrolment and four-month intervals in accordance with the WHO guideline [26].

#### *Praziquantel*

Praziquantel is a trematodicide used for oral treatment of infections due to schistosome and liver fluke. Praziquantel induces a rapid contraction of schistosomes by a specific effect on the permeability of the cell membrane. The drug further causes vacuolization and disintegration of the schistosome tegument. After oral administration praziquantel is rapidly absorbed (80%), subjected to a first pass effect, metabolized and eliminated by the kidneys. Maximal serum concentration is achieved one to three hours after dosing. The half-life of praziquantel in serum is 0.8 to 1.5 hours. However, in patients with moderate-to-severe hepatic dysfunction (Child-Pugh class B and C), praziquantel half-life, C max, and AUC increased progressively with the degree of hepatic impairment. In patients with schistosomiasis the half-life is 2.99 hour ± 1.28, the T max is 1.48 hour ± 0.74, the C max is 0.83 μg/mL ± 0.52 and the AUC is 3.02 μg/mL hour ± 0.59 (34). Praziquantel will be given at 40 mg/kg at enrolment and at the twelve-month follow-up [33].

### Concomitant treatments

The administration of paracetamol (acetaminophen) is allowed if the patient’s condition warrants it and should be recorded in the appropriate section of the CRF. Drugs with antimalarial activity (such as co-trimoxazole, macrolides, tetracycline or doxycycline) should be reported as concomitant medications. All concomitant medications taken by the patient during the study, from the date of signature of the informed consent are recorded in the appropriate section of the CRF.

### Safety assessment

Safety and tolerability of the treatments are evaluated by recording AEs and grading, laboratory, and vital signs evaluations [34]. All AEs are recorded and classified in accordance with their severity, seriousness, relationship and outcome. The severity of a clinical AE is scored as: mild when the patient is aware of the sign or symptom, but it is easily tolerated; moderate when the discomfort is enough to cause interference with usual activity; severe when the event causes incapacity with inability to work or perform usual activity; and life-threatening when the patient is at risk of death at the time of the event.

The investigators assess the drug-event relationship of each AE/SAE by using clinical judgment. Alternative causes, such as natural history of the underlying conditions or diseases, concomitant therapy, other risk factors and the temporal relationship of the event to the investigational product are considered and investigated. The investigator also consults the drug information and the Data and Safety Monitoring Board as needed in the determination of his/her assessment. For every AE, it is very important that the investigator always make an assessment of causality prior to transmission to the Trial Management Group even if the investigator disposes of minimal information to include in the initial report to the Trial Management Group. The investigator may change his/her opinion of causality in the light of follow-up information, amending the SAE case report form accordingly.

The outcome of each AE must be assessed according to the following classification: completely recovered, not yet completely recovered, deterioration, permanent damage, death, ongoing, or unknown.

All serious AEs, whether or not deemed drug-related, or expected, must be reported immediately or within 24 hours (one working day), using the Serious Adverse Event Notification Form by telefax or email to the sponsor. The report should state “Urgent Serious Adverse Event” and highlight the study code on the cover page. All other AEs not fulfilling the criteria of immediate reporting are recorded on the Case Report Form. This AE information is collected on a regular basis during the clinical trial.

### Statistical analysis plan

The effect of the type of intervention (either IPT versus the controls, or SP versus SP-P) will all be analysed using linear mixed model analysis. In each analysis, Hb concentration is modeled versus time, testing whether the change of Hb concentration over time differs between the two types of intervention. In each case, a linear mixed model is fitted with Hb concentration as outcome variable, and fixed effects including the type of intervention (indicator variable), time and the interaction between them. In these models, the effect of interest is the interaction between intervention and time, which formally tests the null hypothesis that the change in Hb concentration with time is the same in all interventions. Significance of the interaction term is tested using the F-test with a Kenwardroger correction for the number of degrees of freedom. As the study includes several (longitudinal) measurements within the same individual, and since the individuals cluster within schools, the dependency between individuals will be accounted for by including random effect terms into the model. More particularly, the model will include random effects (intercept and slope) for individual, nested within the random effect of school. An additional advantage of this technique is that it gives unbiased results in case individuals are lost to follow-up during the study.

Analysis of the data will be performed using the nlme package from the statistical software R or the proc mixed procedure from the software package SAS. All statistical analyses will be performed in close collaboration with StatUa, the Center for Statistics at the University of Antwerp.

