### Design and sample size calculation

The study is an unblinded, randomised controlled trial, enrolling asymptomatic school children, either gender. At baseline, month four, and month eight, IPT with SP or SP-PQ is given. SP is administered as a single treatment dose. However, PQ is given as two doses with a 24-hour interval. IPT is administered at four month intervals in line with the long half-lives of the drugs and for compliance. Each treatment arm will be compared to the control group of untreated participants. Due to the prevalence of STH and schistosomiasis in the study area all participants are treated with albendazole or praziquantel according to the WHO guidelines [26]. Before the study, parents or guardians and children were informed about the objectives and the design of the study during organised meetings at schools.

Within each school, each schoolchild is randomly assigned to one of the two intervention groups or the control group as follows: IPT-SP, IPT-SP-PQ and no-treatment. Each study arm consists of one-third of all individuals.

To estimate the statistical power of our studies, we used an effect size of 0.56 g/dl mean Hb level improvement by the antimalarial IPT compared to the control treatment. This effect size was based upon a previous study.

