A previous study estimated the mean Hb concentration of 13.01 g/dl respectively in schoolchildren with IPT and 12.45 g/dl without [27]. The sample size of the study is all schoolchildren of two schools selected within the nearest schools to the regional hospital centre. The overall number of schoolchildren in the two schools is estimated to be 1,300 (650 in each school). By excluding 200 children of the sixth primary school year (100 per school), and accounting for 20% cancelation and 30% to 40% absenteeism, a realistic sample size of 616 individuals is reached for the complete IPT treatment schedule. Using this effect size and sample size, power estimates were performed by Monte Carlo simulation. In each run, a dataset was simulated assuming the within-subject variance and between-subject variability was 16, and putting in effect size to 1. The power was then estimated by fitting a linear mixed model to the data (Hb level versus treatment, time and time:treatment interaction) and testing the significance of the interaction term. The power is then equal to the fraction of times the interaction term was significant, using a significance level of 5%. A sample size of 616 offers 100% power to detect superiority between the control and the intervention groups. For the non-inferiority of SP versus SP-PQ, this sample size has over 91% power to detect a difference in effect less than 0.27 g/dl (<50%).

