### Treatment administration

The study treatment is administered under the direct supervision of a study nurse. Study drugs are given to the children consistent with the investigational brochure of each product. After drug administration, children will be kept for thirty minutes in the class. In case vomiting occurs within 30 minutes of administration a dose is repeated in full. This event is documented in the CRF. If vomiting persists beyond two additional doses, the child is withdrawn from the study.

Upon arrival at a school, an inventory is performed and a drug receipt log filled out and signed by the staff. Accountability for the drug at all school sites is the responsibility of the principal investigator. The investigators ensure that the drug is used only in accordance with this protocol. Accountability records include dates, quantities, lot numbers, expiration dates, and patient numbers.

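### SP versus SP-PQ is powered as a non-inferiority comparison at 0.27 g/dl but analysed with an F-test of no difference, which cannot support that claim

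*Protocol article*

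**What the plan says.** Design and sample size calculation sets the superiority target: "we used an effect size of 0.56 g/dl mean Hb level improvement by the antimalarial IPT compared to the control treatment". It then gives the comparison of the two active regimens a different aim: "For the non-inferiority of SP versus SP-PQ, this sample size has over 91% power to detect a difference in effect less than 0.27 g/dl". The 0.27 g/dl works as a margin, a little under half of the superiority effect.

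Statistical analysis plan covers both kinds of comparison with one approach: "either IPT versus the controls, or SP versus SP-P) will all be analysed using linear mixed model analysis". For each comparison, a linear mixed model has intervention, time and their interaction as fixed effects. The interaction is the effect of interest, its null is equal Hb change over time, and it is tested with an F-test. The section mentions neither 0.27 g/dl, nor a confidence limit, nor a rule for concluding non-inferiority. It names no analysis set. On incomplete data it says only that the model has the advantage that "it gives unbiased results in case individuals are lost to follow-up during the study".

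The planned number is reached by "accounting for 20% cancelation and 30% to 40% absenteeism, a realistic sample size of 616 individuals is reached for the complete IPT treatment schedule". Under follow-up visits at months 4, 8 and 12, absent children are to be seen on another day of the week for treatment and blood sampling.

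**The concern.** Superiority and non-inferiority test different nulls. For IPT versus control, the null is no difference, and rejecting it supports the claim. For non-inferiority, the null is a deficit of at least 0.27 g/dl, and the claim needs that deficit to be excluded. An F-test of no difference does not do this. If it is non-significant, the data may still be compatible with a deficit above 0.27 g/dl. If it is significant, the deficit may still be well inside the margin, or the difference may favour the regimen under test.

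The analysis as written therefore leaves no valid route to the conclusion for which the study is said to have 91% power. The likely substitute, reading a non-significant interaction as showing that the regimens are equally good, errs in the unsafe direction. Imprecision and missed doses both make non-significance easier to obtain. The document itself allows for 30% to 40% absenteeism.

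**Working it through.** **The two sections side by side**

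| | Design and sample size calculation | Statistical analysis plan |
|---|---|---|
| Aim for SP versus SP-PQ | Non-inferiority | Whether Hb change over time differs |
| Null | Deficit of 0.27 g/dl or more (implied) | No difference |
| Criterion | 0.27 g/dl | Significance of the F-test |

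**The plan's own figures**
- Margin as a share of the superiority effect: 0.27/0.56 = 0.482, which agrees with the stated figure of under 50%.
- Sample size: 1,300 − 200 = 1,100; × 0.80 = 880; × 0.70 = 616. This reproduces exactly. At 40% absenteeism it is 880 × 0.60 = 528.
- Power over 91%: not reproduced from the stated inputs. With about 205 children per arm, a simple two-mean test with SD 4 (variance 16) gives 10% at one-sided 2.5% and 17% at one-sided 5%. A slope model with visits coded 0 to 3, residual variance 16, no random-slope variance and margin 0.27/0.56 gives 78% to 86%. The units of the variance and effect size are not given, so this check is inconclusive.

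**What the F-test would conclude, taking 91% at face value**

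The sidedness of the non-inferiority test is not stated; one-sided 2.5% is assumed.
- Implied standard error: SE = 0.27/(1.960 + 1.341) = 0.082 g/dl.
- The F-test is non-significant when the estimated difference is below 1.96 × 0.0818 = 0.160 g/dl in either direction.
- Non-inferiority needs estimate + 1.96 × SE < 0.27, so the estimated deficit must be below 0.27 − 0.160 = 0.110 g/dl.
- An estimated deficit between 0.110 and 0.160 g/dl is therefore non-significant but does not show non-inferiority. At 0.160 the upper limit is 0.160 + 0.160 = 0.320 g/dl.
- If the true deficit equals 0.27 g/dl, the chance of a non-significant F-test is 1 − Φ(0.27/0.0818 − 1.96) = 0.09. The margin-based rule would wrongly claim non-inferiority with probability 0.025.
- With less precision the gap widens. If, for illustration, the SD were 1.6 g/dl with 205 per arm, SE = 1.6 × √(2/205) = 0.158 and the chance of non-significance at a true deficit of 0.27 is Φ(1.96 − 0.27/0.158) = 0.60.

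**Missed doses (illustrative only)**

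Suppose the true difference under full dosing is 0.27 g/dl, SE is 0.082, a share p of the analysed children is under-dosed, and each of them loses a share q of the between-regimen difference. The diluted difference is d = 0.27 × (1 − pq). The chance of a non-significant F-test is Φ(1.96 − d/SE). The chance that even a margin-based rule claims non-inferiority is Φ((0.27 − d)/SE − 1.96).

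| p | q | d (g/dl) | F-test non-significant | Margin rule claims non-inferiority |
|---|---|---|---|---|
| 0 | – | 0.270 | 9% | 2.5% |
| 30% | 1/3 | 0.243 | 16% | 5% |
| 30% | all | 0.189 | 36% | 17% |
| 40% | 1/3 | 0.234 | 18% | 6% |
| 40% | all | 0.162 | 49% | 26% |

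Neither p nor q is in the document. Setting p to the absenteeism allowance gives an illustration, not a forecast. The SE also rests on the unreproduced 91%. If it is scaled to 880 children (0.0818 × √(616/880) = 0.068), the margin-rule column runs from 6% to 35% for the four diluted rows.

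**The case against.** The strongest objection is that an article condenses the protocol, and a full analysis plan may hold the non-inferiority rule and the analysis sets. For the analysis sets this stands: the lack of a per-protocol population here is not an error. It does not dispose of the main point. The section does not stay silent on SP versus SP-PQ; it assigns that comparison an F-test of equality, which conflicts with the aim in the sample size section.

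A reader might go further and infer that the plan fixes a single all-children model for both questions, so that 30% to 40% missed dosing will push the result to non-inferior. The document does not support that:
- No analysis set is named. The remark on loss to follow-up and the short list of withdrawal criteria suggest that partly treated children stay in. But 616 is described as the number with the complete schedule, which could equally suggest completers.
- A model is fitted for each comparison, so 'single' is inaccurate.
- Absenteeism is not missed dosing. Catch-up visits recover dose and Hb together, and a child never reached at a visit contributes no Hb value there. Some under-dosed children could still be measured, for example after missing only the second piperaquine dose, but their number is unknown.
- A child who misses one course has still received a different regimen, so loss of the whole difference is an extreme case.

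One might also ask that non-inferiority be claimed only if a fully dosed set agrees. That set is defined after randomisation, and its dose criteria differ between arms, so it is better used as support than as a condition.

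**Conclusion.** The concern holds as a mismatch between aim and test. Non-inferiority of SP versus SP-PQ at 0.27 g/dl is powered, but the stated analysis tests equality and cannot establish it. This follows from the text and needs no assumption.

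Its numerical size is conditional. On the stated 91% power and a one-sided 2.5% level, taking non-significance as non-inferiority would be wrong about 9% of the time at a true deficit equal to the margin, against 2.5% for a margin-based test. The rate is higher if precision is worse than claimed. With the SE scaled to 880 children it would be about 2.4%, close to the margin-based rate, but the F-test would still be answering the wrong question.

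The effect of missed doses is a secondary remark. Its direction is clear if under-dosed children are analysed. Its size cannot be determined from the document. The correction should be made before analysis.

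**What to change.** In Statistical analysis plan, separate the two comparisons.

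1. IPT versus control: keep the F-test of the intervention-by-time interaction.
2. SP versus SP-PQ: from the same mixed model, estimate the month-12 difference in Hb change with its confidence interval. Claim non-inferiority only if the relevant confidence limit lies within 0.27 g/dl in all randomised children. State the confidence level and which regimen is being tested against which. State that a non-significant F-test is not evidence of non-inferiority.
3. Supporting analysis: report the same estimate in children who received every scheduled dose (three courses, with both piperaquine doses in the SP-PQ arm), adjusted for baseline Hb, age and school. If the two estimates disagree, interpret the claim cautiously.

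The cost is a few sentences and one more fit of the same model. Doses are given under a study nurse's supervision and dispensing is recorded, so fully dosed children should be identifiable without new data collection. The downside is that the claim becomes harder to reach, and the supporting set is not protected by randomisation. Any figures for inflation due to missed doses should be labelled illustrative.

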### Endpoints

#### *Primary endpoint*

The primary endpoint is the change in mean Hb concentration at month 12 of follow-up and anaemia prevalence one year after the initial preventive treatment.

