#### *Secondary endpoints:*

1. Change in mean Hb concentration at month 4 and 8 of follow-up.

2. Prevalence of asymptomatic and clinical malaria at baseline and one year after enrolment.

3. Prevalence of *pf*DHFR and *pf*DHPS gene mutations at baseline and at month 12 follow-up.

4. Clinical (severe) malaria incidence and parasitaemia at month 4, 8 and 12.

5. Percentages of acute and severe malnutrition at month 0, 4, 8, 12 through weight/height and height/age z-scores, and skin folds.

6. School achievement at the end of follow-up and school attendance.

7. Prevalence and risk of environmental and host-related predictors for malaria (re)infections.

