### Randomisation and treatment allocation

Children fulfilling the inclusion/exclusion criteria will be assigned a sequential study number and will be treated according to a predetermined randomization list of blocks of varying size per school. Within each block each schoolchild will randomly be assigned to one of the two intervention groups or the control group in 1:1:1 balance. Sealed envelopes labeled with the school unique code and containing the list with the treatment allocated to the participants will be provided according to the above mentioned list and opened at the moment the children are recruited.

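### The primary test (intervention-by-time interaction over all visits) is not the primary endpoint (Hb change at month 12), and no month-12 contrast is named

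*Protocol article*

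**What the plan says.** - Primary endpoint section: "The primary endpoint is the change in mean Hb concentration at month 12 of follow-up". Anaemia prevalence at one year is named alongside it and is not at issue here. The Abstract also gives Hb change at 12 months as the primary endpoint.
- Secondary endpoints, item 1: "Change in mean Hb concentration at month 4 and 8 of follow-up". The earlier visits therefore have their own, lower-ranked endpoint.
- Table 1: Hb is measured at baseline and at months 4, 8 and 12.
- Statistical analysis plan: Hb is the outcome, with "fixed effects including the type of intervention (indicator variable), time and the interaction between them". The section continues: "In these models, the effect of interest is the interaction between intervention and time". That term is tested by an F-test with the Kenward-Roger correction. No contrast at month 12 is named, and the section does not say whether the fixed time effect is numeric or categorical.
- Same section, random part: "random effects (intercept and slope) for individual, nested within the random effect of school". There are two schools (Study area), and children are randomised within school from a "predetermined randomization list of blocks of varying size per school".

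**The concern.** The endpoint is a difference between arms at one visit. The test concerns how the arms diverge over the whole year. The two coincide only under a particular shape of the treatment effect.

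Nothing in the article supports a straight line. Treatment is given in pulses at baseline and months 4 and 8, no Hb time course is given, and the 0.56 g/dl used for the power calculation is a difference between mean levels and not a rate. If the effect is not linear, the headline estimate and p-value describe something other than the declared endpoint. Part of a real effect can then appear as a baseline difference between randomised arms. It would also be unclear after unblinding of the results whether the slope or a month-12 comparison is the primary result.

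The section relies on the mixed model for unbiased results when children are lost to follow-up. That too requires the mean over time to be correctly specified.

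**Working it through.** **Inputs.** Visits are at 0, 4, 8 and 12 months (Table 1). The sample size section gives 616 children, reproduced as 1,100 x 0.8 x 0.7 = 616. Allocation is 1:1:1, so n = 616/3 = 205.3 per arm. Within- and between-child variances are both taken as 16, the figure in the sample size section, so the within-child correlation is 0.5. The units of that 16, and of the effect of 1 simulated with it, are not stated. The article's 100% power therefore cannot be reproduced without guessing, and the standard errors below serve only to compare analyses with each other. The random slope is left out of these formulas.

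**What a linear-time interaction estimates.** Mean time is 6 and the sum of squared deviations is 36 + 4 + 4 + 36 = 80. The arm difference in 12 x slope weights the visit-specific arm differences by 12 x (t - 6)/80, that is -0.9, -0.3, 0.3, 0.9. The effect profiles below are assumed.

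| Effect at months 0, 4, 8, 12 | 12 x slope | Share of month-12 effect |
|---|---|---|
| 0, 1/3, 2/3, 1 (linear) | -0.1 + 0.2 + 0.9 = 1.00 | 100% |
| 0, 1, 1, 1 (full by month 4, held) | -0.3 + 0.3 + 0.9 = 0.90 | 90% |
| 0, 1, 0.5, 0.5 (halves after month 4) | -0.3 + 0.15 + 0.45 = 0.30 | 0.30/0.5 = 60% |
| 0, 0.5, 1, 1 (half, then full) | -0.15 + 0.3 + 0.9 = 1.05 | 105% |

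In the second row the fitted arm difference at month 0 is 0.75 - 6 x (0.90/12) = 0.30 of the effect. With 0.56 g/dl, that assigns 0.30 x 0.56 = 0.17 g/dl to a baseline difference that does not exist.

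**If time is categorical.** With two groups and four visits the interaction has (2 - 1) x (4 - 1) = 3 df. The F-test asks whether the arms differ in change at any of months 4, 8 or 12. It can be significant because of month 4 alone.

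**Precision, arm versus control.**
- Simple change, month 12 minus month 0: sqrt(2 x 32/205.3) = 0.558.
- 12 x slope with free baseline, as written: sqrt(2 x (144 x 16/80)/205.3) = sqrt(2 x 28.8/205.3) = 0.530.
- Month-12 contrast with common baseline mean: sqrt(2 x 32 x (1 - 0.5^2)/205.3) = sqrt(48/205.3) = 0.483.
- 12 x slope with common baseline mean: with x = (0, 1/3, 2/3, 1), the information is (205.3/2) x (1/16) x (14/9 - 0.2 x 2^2) = 4.85, so SE = 0.454.

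Moving from the slope as written to the month-12 contrast improves precision (0.530 to 0.483), but that gain comes from using baseline Hb. Given the same common baseline, the slope is the more precise of the two (0.454 against 0.483).

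**School.** In a simulated dataset analysed by generalised least squares, the interaction per visit was 0.258 (SE 0.0382) whether school was random (variance 0.1 to 10) or fixed. With 15% of follow-up visits missing it was 0.2405 (SE 0.0404) either way.

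**The case against.** The strongest defence is that the interaction is a valid test, under randomisation, of no difference in change over time, and that the sample size section powers the same term. Time coding, covariance structure and a named contrast could sit in a fuller plan that is not shown. The validity point stands. The last point does not dispose of the matter, because the article does state the effect of interest, and what it states differs from the endpoint on either coding of time.

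Some stronger conclusions are tempting and should not be drawn.

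- **That the slope test has less power.** A reader might infer this from 0.530 against 0.483. The documents do not support it as a property of the slope. Against the simple month-12 change the slope is more precise (0.530 against 0.558). An 80% power for the simple change becomes 84% for the slope if the effect builds linearly, and 76% if it is full by month 4 and held. With a common baseline the slope is also more precise than the month-12 contrast.
- **That the discrepancy is always large.** A common-baseline slope gives 106% of the month-12 effect for the plateau and 97% for the halving profile, so much of the 90% and 60% comes from the free baseline term.
- **That the effect will plateau or wane.** No Hb trajectory is given. Repeat dosing leaves a cumulative gain equally open, and the third non-linear profile overstates the effect slightly.
- **That time is certainly linear.** The random slope and the modelling of Hb against time point that way, but a random slope can be combined with categorical fixed time.
- **That the two-level school effect distorts the primary result.** Randomisation is within school and the interaction is a within-child contrast, so estimate and SE are unaffected.

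**Conclusion.** The mismatch between endpoint and test is real. On the natural reading the primary test targets an average slope, and on the other reading a 3-df joint hypothesis. Neither is the Hb change at month 12. How far the slope departs from the endpoint depends on an effect profile that the article does not give: 90%, 60% and 105% of the month-12 effect in the three non-linear profiles tried. These are illustrations, not predictions.

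The case for a month-12 contrast is that it estimates the declared endpoint without assuming linearity. The precision figures assume equal within- and between-child variances and no random slope. They do not show that using a slope costs power. With only two schools the school variance can barely be estimated, so a fixed effect is tidier, but that is a minor matter.

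**What to change.** State in the Statistical analysis plan, before the data are analysed:

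1. Hb at months 0, 4, 8 and 12 is modelled with visit as a four-level factor, arm-by-visit terms at months 4, 8 and 12, and one common baseline mean across arms (or adjustment for baseline Hb).
2. The primary Hb test is the 1-df arm-versus-control contrast at month 12.
3. The month-4 and month-8 contrasts from the same fit serve secondary endpoint 1.
4. School, which is the randomisation stratum, is a fixed effect (minor).

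If the sponsor does want the yearly slope as the primary quantity, the primary endpoint should be reworded to say so and the linearity assumption stated.

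The change needs no new data and only revised wording. In a two-group comparison the mean model goes from 4 parameters (intercept, arm, time, interaction) to 7 (four visit means, three arm-by-visit terms), before school, which is trivial with about 600 children. The other cost is some precision relative to a baseline-constrained slope: SE 0.483 against 0.454, about 6% larger (0.483/0.454 = 1.06).

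### The primary Hb model leaves each arm its own baseline mean and tests only the interaction: valid, but less precise than the collected baseline data allow

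*Protocol article*

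**What the plan says.** The Statistical analysis plan section fits a linear mixed model to Hb with "fixed effects including the type of intervention (indicator variable), time and the interaction between them". It then states that "the effect of interest is the interaction between intervention and time". For the random part, "the model will include random effects (intercept and slope) for individual, nested within the random effect of school". The same model is used for IPT versus control and for SP versus SP-PQ.

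Table 1 schedules Hb at baseline and months 4, 8 and 12, so baseline Hb enters as one of the repeated outcomes. No baseline covariate and no shared baseline mean is stated. The power simulation in Design and sample size calculation lists the same three fixed terms, "assuming the within-subject variance and between-subject variability was 16, and putting in effect size to 1".

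Randomisation and treatment allocation uses blocks within school: "Within each block each schoolchild will randomly be assigned to one of the two intervention groups or the control group in 1:1:1 balance".

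**The concern.** Individual randomisation makes the true baseline Hb means of the arms equal. The intervention main effect therefore estimates a quantity known to be zero. With that term free, the interaction becomes a contrast of change from baseline. The efficient use of baseline Hb subtracts only the part of the baseline difference that predicts later Hb.

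Two things are at stake. The standard error of the primary estimate is larger than it need be. And in any one trial where an arm happens to start low, that arm will tend to appear to gain more. Both comparisons are affected. SP versus SP-PQ matters most, because its stated power (over 91%, for a limit of 0.27 g/dl) leaves room to gain, whereas superiority power is stated as 100%.

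**Working it through.** **Inputs.** Visits at t = 0, 1/3, 2/3, 1 year (Table 1). Within- and between-subject variance both 16, which is one reading of "the within-subject variance and between-subject variability was 16". Total 616, one-third per arm, so about 205 per arm. Effect 0.56 g/dl, set to 1 in the simulation; non-inferiority limit 0.27 g/dl; 5% level, taken as two-sided. The random-slope variance s and the time coding are not given.

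**The plan's own power first.** Each child's fitted slope has variance 16/Sxx, with Sxx = 2(0.5² + (1/6)²) = 0.556, giving 28.8 per year². Coding time by visit (0 to 3) divides this by 9, giving 3.2.
- Superiority, effect 1 per visit, 205 per arm: SE = √(2 × 3.2/205) = 0.177; 1/0.177 = 5.66; power 99.99%. This matches the stated 100%.
- Non-inferiority, limit 0.27/0.56 = 0.482 per visit: at 205 per arm, 0.482/0.177 = 2.73, power 77.9%. At 308 per arm (616 split over two arms), SE = 0.144, ratio 3.34, power 91.7%. Of the codings and arm sizes tried with variances of 16, only this one matches the stated figure.

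**Variance with and without the free baseline mean (s = 0).**
- Linear time: intercept variance 16 + 16(1/4 + 0.25/0.556) = 27.2; covariance with the slope −16 × 0.5/0.556 = −14.4. Free baseline 28.8; common baseline 28.8 − 14.4²/27.2 = 21.2. Ratio 0.735, a cut of 26.5%.
- Month-12 contrast, categorical visits: change variance 32; covariance with baseline −16; baseline variance 32. Common baseline 32 − 16²/32 = 24. Ratio 0.75, a cut of 25%. A simulation of change score against baseline-adjusted analysis (4,000 runs, 205 per arm) gave 0.740.

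**Sensitivity.**

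| Assumption | Linear time | Month-12 contrast |
|---|---|---|
| Both variances 16, s = 0 | 26.5% | 25% |
| s = 8 (assumed) | 21% | 20% |
| s = 16 (assumed) | 17% | 17% |
| 16 read as between-subject SD (variance 256), s = 0 | 2.7% | 2.9% |

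With s = 0, other intraclass correlations give a month-12 cut of 35% at 0.3 and 15% at 0.7.

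**Effect on SP versus SP-PQ** (per-visit coding, limit 0.482, s = 0). The common-baseline slope variance is 21.2/9 = 2.35.
- 205 per arm: SE 0.177 to 0.152, power 77.9% to 88.9%.
- 308 per arm: SE 0.144 to 0.124, power 91.7% to 97.4%.

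**Changing the time term as well.** If the plan's time is linear, moving to a month-12 contrast gives back part of this gain: 28.8 to 24, a net cut of 17%. On the same scale the limit at month 12 is 3 × 0.482 = 1.446. At 205 per arm SE = √(2 × 24/205) = 0.484, ratio 2.99, power about 85%.

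**The case against.** The strongest reply is that nothing here is wrong. The primary endpoint is a change in mean Hb at month 12, and an intervention-by-time test in a mixed model is a standard, valid way to test it. That stands. A reader might infer that regression to the mean biases the primary result. It does not: the distortion exists only conditional on a chance baseline imbalance, and it averages out over randomisations.

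A second reply is that the fixed-effects list is introduced as inclusive, so a fuller plan could add baseline Hb. That is possible. But the section goes down to the tested term and the degrees-of-freedom correction, and the power simulation lists the same three terms with no baseline adjustment.

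Third, the quarter is not computed from the full planned model, which has a random slope, and it depends on an ambiguous variance phrase. Both points stand, so the figure has to be given as a range.

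Fourth, a reader might infer a large gain in superiority power. If the effect is a total month-12 difference of 1 g/dl, power at 205 per arm goes from 47% to 59%. The documents do not state that coding, and the coding that reproduces their 100% leaves nothing to gain there.

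Last, a common intercept with linear time is not assumption-free. It also requires the arm difference to grow linearly from zero. For an effect δ reached by month 4 and then held, the free model estimates 0.90δ. The constrained model gives 0.90δ + (14.4/27.2) × 0.30δ = 1.06δ, where 0.30δ is the fitted intercept difference. This stands and shapes the fix.

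**Conclusion.** The point holds as a loss of precision in a valid analysis. It is not an error of inference. With both variances at 16, the stated model gives up about 25% of the variance of the treatment effect without a random slope, and about 17-21% with assumed slope variances of 8-16. The loss falls to about 3% if 16 is a between-subject SD. These ratios depend on the relative variance components and the visit times, not on effect size, time units or arm size.

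The power consequences are less firm, because they need a time coding and, for the stated 91%, an arm size that the text does not give. On the coding that reproduces the stated power, SP versus SP-PQ gains about 11 points at 205 per arm (78% to 89%) or about 6 at 308 (92% to 97%), both with linear time and no random slope. If superiority power is truly 100%, that comparison gains precision only. The change is worth making because it uses data already collected and relies on the randomisation.

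**What to change.** In the Statistical analysis plan section:
- Treat visit as categorical (0, 4, 8, 12 months) and keep baseline Hb as an outcome row.
- Give the arms one baseline mean, with no intervention effect at time 0.
- Test the month-12 intervention contrast, in the same form for IPT versus control and for SP versus SP-PQ.

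An alternative is to model months 4, 8 and 12 with baseline Hb as a covariate. The tested term must then be the month-12 intervention difference. The post-baseline interaction would not do: an effect reached by month 4 and held would give an interaction of zero, and the per-child slope variance would be 16/(2/9) = 72 against 28.8.

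If linear time is kept, state that the common intercept also assumes the arm difference grows linearly from zero.

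Re-run the power simulation with the chosen model, stating the variance components (including any slope variance), the time coding and the arm sizes. The cost is a small change of wording and code and one simulation re-run. No extra children, visits or measurements are needed, and the software already named can fit the model.
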